**Figure 3 F3:**
[figure not shown]
**Outcomes of the trial**. *EmOC: Emergency obstetric care.

### Randomization and allocation

Centres were included on the basis of formal, informed consent on the part of the hospital director and the person in charge of maternity services. After a one-year pre-intervention data collection phase, each hospital was randomly assigned, in August 2008, to either an intervention group, in which the AIP will be implemented, or a control group.

The participating hospitals were stratified in six strata corresponding to the combination of two countries (Mali and Senegal) and three hospital types: hospitals in the capital, regional hospitals, and district hospitals outside the capital. We attempted to ensure optimal balance between the hospitals assigned to the intervention and the control groups in terms of their number and size (number of deliveries per year). Therefore, within each stratum, we first ranked the hospitals with respect to size, and then used blocked randomization, with each block of size two containing two hospitals with adjacent ranks, i.e., of similar size (Figure 4). All participating hospitals were randomized simultaneously, after their list was provided, which eliminated any risk of allocation bias.

**Figure 4 F4:**
[figure not shown]
**Trial design**. *The hospitals in each country's capital (Dakar in Senegal and Bamako in Mali) are characterized by a high level of obstetric activity (more than 3000 deliveries annually) and are easily accessible to the public because of their proximity. °Regional hospitals and district hospitals are outside the capitals. ^+^Randomization by blocks of 2 in order to ensure a comparable number of patients in both groups.

### Data collection and management

#### Data collection

A system of data collection, independent of the AIP, was set up in September 2007 in the 46 study hospitals. This system is based on the WHO global survey on maternal and perinatal health [20], which considers clinical data at the individual level and organizational data at the facility level. All deliveries carried out in the participating centres are registered by local collectors (nurses or midwives trained to do this). These collectors complete a standard form for each eligible patient that includes information on maternal characteristics, prenatal care, labour and delivery, diagnosed complications, and the vital status of both mother and child at discharge from hospital (see patient registration form, Additional file 1). This information is extracted from the hospital registers and from available medical records whose quality and archiving are regularly monitored by the national coordinator of the study. These data will be collected on an ongoing basis throughout the study. With respect to facility-level data, the national coordinator carries out an annual inventory of the resources available in each hospital using a standardized grid, by visiting all the services of the hospitals involved in EmOC.

To assess the quality of care, we will sample medical records of 50 patients at each of the 46 participating centres using simple random sampling. An external evaluator will assess each record using a criterion-based clinical audit (CBCA) to obtain a score for quality of care. The CBCA scores, ranging from 0 to 27, are then dichotomized as standard (score equal to or greater than 22) versus sub-standard (score below 22) care. The sample size of 50 records/centre will allow us to estimate the proportion of patients receiving standard care in each centre with sufficient precision. Specifically, the half-width of the 95% confidence interval will not exceed 15%. The CBCA developed by the researchers of the QUARITE trial employs evidence-based clinical criteria to ascertain if minimal quality of care is provided to the patients sampled. These criteria have been selected based on thorough review of the literature and expert consensus and are consistent with the WHO guidelines for conducting an obstetrical CBCA (Beyond the numbers: Reviewing maternal deaths and complications to make pregnancy safer. Geneva: World Health Organization, 2004) [15].

Before, during, and after the intervention period, satisfaction surveys will be conducted with all the health professionals in the participating centres; these will be done by a research professional in individual interviews. We will use a pre-tested questionnaire that contains 42 closed, Likert-type questions. The questions on satisfaction relate to remuneration, work tools and environment, work organization and content, training and supervision, emotional satisfaction, management style, and attitudes toward change. As part of these surveys, staff censuses are undertaken in all the health facilities included in the study.

### Data management

Patient records are collected by the national coordinator during quarterly visits and transferred to the national coordinating centre for double data entry using Epi-Info 2000 software. The electronic record, cleared of each quarter's clinical data, is then transmitted to the trial's coordinating centre at the University of Montreal and stored in a secure location. The facility-level data and the data regarding staff satisfaction are recorded separately. The different databases are periodically verified by the data manager. All information collected on patients, health professionals or facilities is confidential. Access to the clinical database is restricted to the data manager until the end of the study. Access to the other databases is restricted to the coordinators and researchers responsible for the various sections of the trial.

#### Quality control of data

The quality control of clinical data will be carried out in three stages. The first stage corresponds to the quarterly visits of the national coordinator. During these visits, the coordinator verifies that the data collection is exhaustive by comparing the number of eligible patients on the hospital's birth register with the number of patient forms collected. A complementary procedure is carried out to monitor the thoroughness of data on maternal deaths, which are generally under-registered in the maternity ward, by identifying the eligible maternal deaths among all the female deaths that occurred in the facility using the various registries available: admissions, hospitalizations (maternity and other services), operating rooms, and morgue. On a random sample of patient forms, the coordinator checks the quality of data collected. The completion rate will be estimated as the proportion of patient forms that contain 100% of the following information: date of entry, patient identification, date of discharge, and vital status of the mother at the date of discharge. The concordance rate will be estimated as the proportion of patient forms whose information is concordant with the hospital registers and medical records. Both the completion rate and the concordance rate are expected to be above 75%. If the completion or concordance rate is between 50% and 75%, the coordinator will check the data quality on a new random sample of patient forms. A completion or concordance rate of less than 50% will trigger the verification of all patient forms. A second control of missing or abnormal data will be carried out at the national coordination centres before data entry. If necessary, the missing information is obtained from the collectors of each facility by telephone or fax. The third step is carried out by the data manager after the data has been entered and transmitted to the trial coordination centre. An audit report of the database, including lists of duplications and missing or abnormal data, is sent quarterly to the national coordination centres, which are responsible for correcting any errors.

### Statistical analysis plan

#### Sample size and power calculations

The formula for calculating the required number of patients is that used for a cluster-randomized controlled trial design [21]. The calculation is based on an overall maternal mortality rate of 1.5% in the pre-intervention phase and an expected reduction of 30% in maternal mortality in the hospitals of the intervention group, in comparison with the control group. This rate was estimated as an approximate average of stratum-specific rates, which ranged from 0.3% to 2.7%, observed in Senegal in a pilot study in 2004-2005 [16]. Taking into consideration a minimum of 830 women included per hospital, the number of patients required was calculated for an odds ratio of 0.70 and for an intra-cluster correlation coefficient (ρ) of 0.001. The value of 0.001 can be considered conservative given the results of the WHO global survey on maternal and perinatal health [22]. The calculation shows that a total of 38,205 patients and 46 hospitals (38,205/830) allows us to achieve a power of 82% to detect a 30% reduction in the overall rate of maternal mortality between the two groups (OR = 0.70) with 2-sided significance test at α = 0.05 and with ρ = 0.001 (ACluster-design^® ^2005, version 2.0, World Health Organization).

According to service statistics available for 2006 and collected for the 46 hospitals in the study, the expected number of deliveries is 96,941 (mean cluster size = 2300; minimum = 830; maximum = 8600), 50,144 in Senegal and 46,797 in Mali. We identified 1,067 trained professionals working in these facilities, 536 in Senegal and 531 in Mali.

#### Type of analysis and handling loss-to-follow-up

The acceptability of the various components of the AIP, including maternal death audits, is high [16,23]. Nevertheless, it is possible that a few hospitals may decide to withdraw from the study. For these hospitals, data collection will continue until the end of the study, in accordance with the commitment made by the hospital authorities at the time of inclusion. These hospitals will therefore not be excluded from the analysis. We will conduct intention-to-treat analyses: each patient will be analyzed in the hospital where she was admitted and each hospital will be analyzed within the group to which it was originally assigned by the randomization.

#### Statistical analyses

Binary outcome (maternal death) will be measured for each woman included in the study, while the unit of randomization and intervention is the hospital, to avoid contamination bias. A first descriptive analysis will allow us to verify, in the pre-intervention phase, the comparability of the groups in terms of the characteristics of the centres and of the patients included. The primary analyses will take into account the inter- and intra-cluster variability and adjust the intervention effect for stratification variables (country and hospital type). To adjust the estimate of variance in the intervention's effect on the interdependence of the events measured (maternal death or not) among the patients of a given hospital, we will use the Generalized Estimating Equations (GEE) approach which generalizes logistic regression to cluster data [24]. The interchangeable structure of the residual covariance matrix will be used to represent intra-cluster correlations. In secondary analyses, we will use the multivariable GEE model to adjust the effect of the intervention for those patient-level or hospital-level variables that show a marked imbalance between the two arms of the trial. The same approach will be used for secondary assessment criteria. In all the analyses, the effect of the intervention will be estimated using the odds ratio (95% CI) from the GEE model and tested by one-tailed Wald testing (α = 0.05) [24].

The preliminary analyses will verify whether the intervention's effect varies according to country using the likelihood ratio chi-square test with one degree of freedom for country-intervention interaction. If the test does not reject the null hypothesis at α = 0.05, the interaction will be eliminated from the final model, which will allow us to assess the overall effect of the intervention. On the other hand, if the interactions are statistically significant, the sub-group analyses will assess the effects of the intervention separately for each country, with a power less than 90%. A similar approach will be used to test whether the effect of the intervention depends: (i) on the overall rate of maternal mortality in the pre-intervention phase (Year 1); (ii) on changes in maternal mortality within the intervention period; or (iii) on hospital type.

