**Methods/Design:**

This is an international, multi-centre, controlled cluster-randomized trial of a complex intervention. The intervention is based on the concept of evidence-based practice and on a combination of two approaches aimed at improving the performance of health personnel: 1) Educational outreach visits; and 2) the implementation of facility-based maternal death reviews.

The unit of intervention is the public health facility equipped with a functional operating room. On the basis of consent provided by hospital authorities, 46 centres out of 49 eligible were selected in Mali and Senegal. Using randomization stratified by country and by level of care, 23 centres will be allocated to the intervention group and 23 to the control group. The intervention will last two years. It will be preceded by a pre-intervention one-year period for baseline data collection. A continuous clinical data collection system has been set up in all participating centres. This, along with the inventory of resources and the satisfaction surveys administered to the health personnel, will allow us to measure results before, during, and after the intervention. The overall rate of maternal mortality measured in hospitals during the post-intervention period (Year 4) is the primary outcome. The evaluation will also include cost-effectiveness.

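### The secondary adjusted models choose covariates by arm imbalance alone, which ignores prognostic value and leaves room for consequences of the programme

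*Protocol article*

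**What the plan says.** All of the relevant analysis text is in the Statistical analyses section of the protocol article.

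- **Primary analysis.** The model will "adjust the intervention effect for stratification variables (country and hospital type"). Both variables are fixed in advance.
- **Secondary analyses.** A GEE model with further covariates is planned. The covariates are to be "those patient-level or hospital-level variables that show a marked imbalance between the two arms of the trial". No requirement of prognostic value is stated, and no limit to variables recorded before allocation.
- **Baseline description.** A separate descriptive step will "verify, in the pre-intervention phase, the comparability of the groups in terms of the characteristics of the centres and of the patients included". The adjustment rule does not refer back to it.
- **Secondary endpoints.** "The same approach will be used for secondary assessment criteria".

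Three facts from other sections matter.

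- **Timing of allocation.** Under Randomization and allocation, "each hospital was randomly assigned, in August 2008, to either an intervention group".
- **Timing of the outcome.** The abstract states: "The overall rate of maternal mortality measured in hospitals during the post-intervention period (Year 4) is the primary outcome".
- **Content of the patient form.** Under Data collection, the form holds "information on maternal characteristics, prenatal care, labour and delivery, diagnosed complications, and the vital status of both mother and child".

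**The concern.** The protocol states a selection rule here, so this is not a detail left to an analysis plan that is not shown. The rule raises two separate difficulties.

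**Wrong criterion.** For a variable fixed before randomisation, a difference between arms arises by chance and carries no information on whether the variable predicts death. What adjustment gains depends mainly on prognostic strength. A rule based on imbalance adds a strong predictor only when it happens to differ between arms. It spends degrees of freedom on variables that differ but do not matter. Because the choice depends on the data, the reported standard error no longer describes the procedure that was followed.

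**No restriction on timing.** The women analysed in Year 4 deliver after the August 2008 allocation, so all of their patient-level data are recorded after allocation. Some of those variables are ones the programme is meant to change. If it changes them, they become imbalanced, and the rule then offers them for adjustment.

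At stake is the reading of the secondary adjusted odds ratios, for mortality and for the secondary endpoints. An adjusted estimate that moves away from the primary one could be taken as evidence about confounding when it has another cause.

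**Working it through.** **Plan's own figure.** The protocol gives no number for this rule. I borrow inputs from Sample size and power calculations, so I checked those first.
- Control rate 1.5% and odds ratio 0.70 give an intervention rate of 1.055%.
- Two-sided α = 0.05 and 82% power give 10,517 women per arm before clustering.
- The design effect is 1 + 829 × 0.001 = 1.829.
- The total is 2 × 10,517 × 1.829 = 38,471, which is 0.7% above the stated 38,205. The inputs are usable.

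**Step 1: how often chance imbalance occurs.** With 23 against 23 hospitals under simple randomisation, the standardised difference of a hospital-level covariate has standard deviation √(2/23) = 0.295. The chance that it exceeds 0.25 in size is P(|Z| > 0.25/0.295) = 0.40. For at least one of ten independent covariates it is 1 − 0.60^10 = 0.99. Randomising in size-ranked pairs lowers this for hospital size and its correlates. The cut-off of 0.25 is my assumption, since the protocol does not say what counts as marked.

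**Step 2: how much a hospital covariate can explain.** A hospital's observed rate varies between hospitals and also by sampling within hospital. The between-hospital share is mρ / [1 + (m − 1)ρ], with ρ = 0.001.
- m = 830: 0.830/1.829 = 0.454
- m = 96,941/46 = 2,107: 2.107/3.106 = 0.678

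If two covariates explain 65% of between-hospital variance (assumed), the R² for the observed hospital rate is 0.65 × 0.454 = 0.295 or 0.65 × 0.678 = 0.441.

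**Step 3: simulation under no effect.** Set-up: 46 hospitals of equal size, 23 per arm; eight independent covariates, two of them prognostic (coefficients in ratio 0.7 to 0.4) and six null; hospital-level linear model; two-sided t-test at 5%; 12,000 runs per row. Outcome variance is scaled to 1. The fixed set is the two prognostic covariates.

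| Women per hospital | Selection cut-off | Fixed set: reported SE | Picked: true SE | Picked: reported SE | Reported SE ratio | Type I error, picked |
|---|---|---|---|---|---|---|
| 830 | 0.25 | 0.252 | 0.280 | 0.298 | 1.18 | 3.7% |
| 830 | 0.50 | 0.252 | 0.289 | 0.301 | 1.19 | 3.9% |
| 2,107 | 0.25 | 0.225 | 0.256 | 0.287 | 1.28 | 2.8% |
| 2,107 | 0.50 | 0.224 | 0.279 | 0.298 | 1.33 | 3.5% |

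The fixed set holds 4.6–5.2%. The unadjusted true SE is 0.294–0.295. With R² = 0 and cut-off 0.25, the picked model has type I error of 4.8%, so the miscalibration disappears.

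**Step 4: adjusting for a consequence of the programme.** Assumed: 20% of control women have a recorded complication, a complication multiplies the risk of death by 15, and the control risk is 1.5%. The risk without a complication is 0.015/(0.80 + 0.20 × 15) = 0.003947.
- *Prevalence falls to 14%, no other effect.* Risk = 0.003947 × (0.86 + 0.14 × 15) = 0.01168. The total odds ratio is 0.78. Adjusted for complication it is 1.00, because risk within each level is unchanged.
- *The same, plus a direct risk ratio of 0.85.* Total 0.66, adjusted 0.84.
- *Recorded prevalence rises to 26%, no other effect.* Risk = 0.003947 × (0.74 + 0.26 × 15) = 0.01832. Total 1.23, adjusted 1.00.

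In each case the adjusted figure is not the total effect of the programme.

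**The case against.** **Only secondary analyses are affected.** This stands in full. The primary covariates are pre-specified. A reader might infer that the main mortality result is biased or loses precision through this rule; the protocol does not support that.

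**The error is in the safe direction.** This also stands. Saying that coverage is not nominal might suggest intervals that are too narrow, but the simulation shows the opposite. The picked model also estimates more precisely than no adjustment (true SE 0.256–0.289 against about 0.295). The loss is relative to a good fixed set.

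**The size could be read as larger.** If two covariates explained 65% of all variance in hospital rates, reported standard errors would be about 50–65% larger and type I error about 2–3%. That leaves too little room for sampling variation within hospitals, given a rare outcome and the protocol's own ρ. The 18–33% range is the one consistent with its inputs.

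**Adjusting for consequences is inferred.** It is. No sentence names complications, mode of delivery, referral or resources as covariates, and Study endpoints treats several of these as outcomes. The baseline comparability check is a natural source for the list. But the rule is not tied to that check. Even if it were, a patient-level variable chosen there would enter the model with Year 4 values. A reader might conclude that the plan does adjust for effects of the programme, or that the bias must run towards no effect. The first is not stated. On the second, an odds ratio of 1.23 moving to 1.00 would hide an apparent harm, not a benefit.

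**Year 4 imbalance may reflect changed case mix.** A fair point: asking whether case mix explains the result is reasonable as a labelled sensitivity analysis. It does not justify imbalance as the general rule.

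**Conclusion.** The point holds for the secondary adjusted models. Selecting by imbalance alone ignores prognostic value and gives conservative inference. The figures of about 3–4% type I error and 18–33% larger reported standard errors rest on two strong known predictors, equal cluster sizes, ρ = 0.001, assumed cut-offs, and a hospital-level linear model in place of the GEE. They are illustrative. With non-prognostic covariates the calibration problem vanishes.

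The open door to variables recorded after allocation is a real weakness in the wording, because the protocol expects the programme to improve resources and quality of care and to reduce severe morbidity. Whether such variables would be chosen is unknown, and the size of any distortion depends on the assumed complication rates. The change is worth making because it costs little. It has no bearing on the validity of the primary test.

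**What to change.** Replace the imbalance criterion for the secondary model with a short covariate list, fixed before outcomes are seen by arm (including for the interim analysis) and used whatever the observed imbalance:

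- **Hospital variables from before randomisation:** Year 1 maternal mortality, annual deliveries and the baseline complexity index. The trial already collects these.
- **Patient characteristics the programme cannot change:** for example age, parity and multiple pregnancy, as far as the patient form records them. The article does not itemise the form, so this needs checking.
- **Exclusions:** diagnosed complications, mode of delivery, referral, later resource inventories and other process variables recorded after allocation.

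Apply the same principle to the secondary endpoints. With 46 hospitals, keep the hospital-level part of the list short.

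The cost is wording; data collection and conduct do not change. The small downside is that an unforeseen imbalance is described, or examined in a labelled sensitivity analysis, and not adjusted for in the main secondary model.

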#### Interim analyses and stopping rules

An independent data security and monitoring committee (DSMC) was established, made up of three international experts in epidemiology and biostatistics, reproductive health research, and obstetrics and gynaecology in resource-poor settings. Its primary responsibility will be to ensure the security of the trial and to monitor the progress of the research according to the established protocol. The committee could decide to stop the trial for the following reasons: if the AIP is proven effective by the end of the first year of intervention; if the quality of the data is inadequate; if the level of implementation of the AIP among the hospitals in the intervention group is too low; if there is significant contamination of the control group; if there is fraud; if there is any new information that would lead to the conclusion that the trial is unnecessary, useless, or even unethical. To assess the effectiveness of the intervention at the end of the first year of intervention, an intermediate analysis will be planned using Peto criteria (α = 0.001), which ensure a total type I risk of error, for the final analysis, of 0.05. If, based on the results of this interim analysis, the DSMC decides to discontinue the trial, we will continue long-term follow-up to monitor the implementation of the program and the reduction of maternal mortality in the two groups (intervention and control).

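### The trial is sized for a two-sided 5% test but analysed with a one-tailed 5% test, which doubles the nominal chance of falsely claiming benefit

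*Protocol article*

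**What the plan says.** Three sections of the protocol article bear on the significance test.

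- **Sample size and power calculations.** The planned number of women and hospitals "allows us to achieve a power of 82% to detect a 30% reduction in the overall rate of maternal mortality" between the groups, "with 2-sided significance test at α = 0.05 and with ρ = 0.001".
- **Statistical analyses.** "In all the analyses, the effect of the intervention will be estimated using the odds ratio (95% CI) from the GEE model", and that effect is to be "tested by one-tailed Wald testing (α = 0.05"). The section extends the same approach to the secondary endpoints.
- **Interim analyses and stopping rules.** An interim look after the first intervention year uses Peto criteria at 0.001, "which ensure a total type I risk of error, for the final analysis, of 0.05". Neither error rate is given a sidedness.

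The article gives no reason for a one-tailed test and does not comment on the change from the sample size section.

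**The concern.** A one-tailed test at 0.05 has the same critical value as a two-sided test at 0.10. The design and the analysis therefore describe different tests of the same hypothesis, and the analysis uses the looser one. Three things follow.

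1. The nominal probability of declaring a benefit that does not exist is 0.05 under the analysis section and 0.025 under the design.
2. The test does not match the 95% confidence interval reported beside it. A two-sided 95% interval corresponds to a one-tailed test at 0.025, so the primary result could be significant by the test and inconclusive by the interval.
3. A difference in the untested direction can never be formally declared, for mortality or for any secondary endpoint.

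The primary conclusion has consequences in the plan itself. Control hospitals are promised the training if the programme proves effective, and the economic evaluation simulates national scale-up. The threshold for calling it effective should not depend on which section is read.

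**Working it through.** **Inputs, all from Sample size and power calculations unless noted**

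- Control rate: "The calculation is based on an overall maternal mortality rate of 1.5% in the pre-intervention phase", so p1 = 0.015.
- Effect and correlation: "calculated for an odds ratio of 0.70 and for an intra-cluster correlation coefficient (ρ) of 0.001".
- Cluster size: "Taking into consideration a minimum of 830 women included per hospital", so m = 830.
- Total 38,205 women in 46 hospitals. Allocation is 23 to 23 (Abstract), so 38,205 / 2 = 19,102.5 women per arm.

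**Step 1. Intervention rate.** The control odds are 0.015 / 0.985 = 0.015228. Multiplied by 0.70 this is 0.010660, so p2 = 0.010660 / 1.010660 = 0.010547.

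**Step 2. Design effect.** 1 + (m − 1)ρ = 1 + 829 × 0.001 = 1.829. The effective number per arm is 19,102.5 / 1.829 = 10,444.

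**Step 3. Expected z.** z = (p1 − p2) / √{[p1(1 − p1) + p2(1 − p2)] / n} = 0.004453 / √[(0.014775 + 0.010436) / 10,444] = 0.004453 / 0.0015537 = 2.866.

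**Step 4. Power under each test**

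| Test | Critical z | Power | Nominal false claim of benefit |
|---|---|---|---|
| Two-sided 0.05 (sample size section) | 1.960 | Φ(2.866 − 1.960) = 81.7% | 2.5% |
| One-tailed 0.05 (analysis section) | 1.645 | Φ(2.866 − 1.645) = 88.9% | 5.0% |

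The two-sided figure reproduces the stated 82%; the one-tailed figure does not. Other ways of computing it leave this unchanged. A Wald test on the log odds ratio gives 81.4% two-sided and 88.6% one-tailed. Reading the 30% reduction as a risk ratio (p2 = 0.0105) gives 82.6% and 89.5%. Solving instead for the total needed for 82% power gives 38,471 two-sided, close to the planned 38,205, and 30,500 one-tailed.

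**Step 5. Observed odds ratio needed to declare benefit.** The standard error of the log odds ratio is √[1/(10,444 × 0.014775) + 1/(10,444 × 0.010436)] = 0.125. The threshold is exp(−1.960 × 0.125) ≈ 0.783 two-sided and exp(−1.645 × 0.125) ≈ 0.814 one-tailed.

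**Step 6. How often test and interval disagree.** Under the assumed effect, the probability of z falling between 1.645 and 1.960 is 88.9% − 81.7%, about 7% (0.0715 before rounding). With no true effect it is 5.0% − 2.5% = 2.5%.

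**Step 7. The same quantity at the expected size.** The article expects 96,941 deliveries, which is 96,941 / 46 = 2,107 per hospital (it prints a mean of 2300). With equal clusters of 2,107 the design effect is 3.106, power is 93.9% two-sided and 96.8% one-tailed, and the gap is about 3%. Cluster sizes run from 830 to 8600, but their coefficient of variation (CV) is not given. Taking the design effect as 1 + [(1 + CV²) × 2,107 − 1] × 0.001, assumed CVs of 0.5, 0.7 and 0.9 give gaps of 4.5%, 5.9% and 7.5%.

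**The case against.** The best defence is that the hypotheses are directional. The Hypotheses section says the programme reduces maternal mortality, and the secondary hypotheses each name a direction too. A one-tailed test fixed in advance is a recognised choice for such a hypothesis. Sizing two-sided and testing one-tailed also leaves the trial with more power than claimed. This shows that one tail could have been argued for. It was not argued for, and the sample size section chose two sides for the same hypothesis.

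Several narrower points stand and limit the concern.

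- Total type I error is nominally 5% under either test. Only the share in the direction of benefit doubles. The interim section's overall 0.05 is therefore compatible with both readings: it neither adds to the contradiction nor resolves it.
- Harm would still be visible, because the confidence interval is reported in every analysis. What is lost is a formal declaration of it.
- The article introduces caesarean section, transfusion, hysterectomy and transfer as interventions considered effective in reducing mortality. It thus implies that more is better, and one cannot simply say these endpoints have no favourable direction. It does not, however, state the tail to be tested for each of them.
- The interaction tests use a likelihood ratio chi-square, so the one-tailed rule covers the intervention effects and not every test in the section.
- The 7% figure belongs to the minimum planned size. At the expected number of deliveries it is roughly 3% to 8%, depending on how unequal the clusters are.

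*One-tailed* may be a slip of wording. As printed, though, it fixes the rule, and an analysis plan that is not shown cannot be assumed to undo it.

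**Conclusion.** The concern holds. The sample size section and the analysis section specify different tests, and the stated 82% power belongs to the two-sided one. As written, the nominal chance of a false claim of benefit is 5.0% where the design implies 2.5%, a factor of exactly 2. The odds ratio needed to claim success moves from about 0.783 to about 0.814 at the planned minimum size. Test and interval give different answers for any favourable z between 1.645 and 1.960.

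These are nominal, large-sample error rates. The power figures rest on the article's inputs (1.5%, odds ratio 0.70, ρ = 0.001, equal clusters of 830) and ignore the interim look, whose effect at 0.001 is negligible. The disagreement between test and interval assumes that the 95% interval is the usual two-sided one. The sample size and the estimator are not affected. The point must still be settled before outcome data are analysed, because it can decide whether the primary result is called positive.

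**What to change.** In Statistical analyses, replace the one-tailed Wald test at α = 0.05 with a two-sided Wald test at α = 0.05 for the primary and all secondary endpoints. A one-sided test at 0.025 would give the same threshold for benefit, but two-sided wording also covers effects in the other direction and matches both the 95% interval and the sample size section.

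In Interim analyses and stopping rules, state the sidedness of the 0.001 and of the overall 0.05. To agree with a two-sided final test, both would be two-sided.

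The cost is one changed sentence and one clarification. Compared with the one-tailed test, power on the planning inputs falls from 88.9% to 81.7%, which is the 82% already claimed. No additional women or hospitals are needed.
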